**Sample Size and Statistical Analysis**

Assuming a two-sided alpha of 0.05, power of 90%, and a 20% drop-out, a sample size of 36 would be needed for each group to detect a between-group mean difference of 1.46 g (SD 1.74) in the reduction from baseline of urine leakage measured by 1-hour pad test according to results of our previous SUI study comparing deep EA with shallow EA[[19](#_ENREF_19)]. We expanded the sample size to 80 cases (40 cases per group) to increase the reliability of the study.

We performed statistical analysis based on the intention-to-treat principle. All patients accepting randomization were included in the analysis. Missing data were filled in by the last observed value. Continuous data were presented with mean and standard deviation [M (SD)] if they were normally distributed, or with median and interquartile range [Median (IQR)] if they were were abnormally distributed. Categorical variables were expressed as numbers and percentages. Student t tests or Mann-Whitney U tests were used for the comparison of continuous variables; chi-square tests, Fisher’s exact tests or Kruskal-Wallis H tests were used to compare categorical variables, as appropriate. For measures collected at two time points, paired t-tests or Wilcoxon signed rank tests were used as appropriate. A statistically significant difference was set at P<0.05. All statistical analyses were performed using SPSS statistical software (version 20.0, International Business Machines Corporation, China).

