**Participants**

The trial is planned to recruit 80 women with pure SUI. Potential participants were guided to finish the laboratory examinations (urine routine, urine flow rate and the residual urine), fill out 72-hour bladder diary and ICIQ-SF, and take 1 hour pad test by research assistants during 1-week baseline assessment to determine eligibility.

Diagnostic criteria are as follows:

1. involuntary urine leakage on effort, exertion, sneezing or coughing, which stopped when the stress ends;
2. visible involuntary leakage from the urethra synchronous with increased abdominal pressure;
3. a pad weight gain >1 g in 1-hour pad test.

Inclusion criteria are as follows:

1. 40 to 75 years of age;
2. meet diagnostic criteria;
3. without symptoms of urinary frequency and urgency.

Exclusion criteria are as follows:

1. met any of the following criteria: other type of UI (urge, mixed, or overflow UI, etc);
2. symptomatic urinary tract infection; ever received UI or pelvic surgery; a severity of pelvic organ prolapse ≥ degree 2;
3. residual urinary volume >30 ml;
4. maximum flow rate ≤ 20 ml/s;
5. limited in walking, stairs climbing and running; receiving specialized treatment for SUI, or taking medicine affecting bladder function;
6. serious cardiovascular, cerebral, liver, kidney, or psychiatric disease, diabetes, multiple system atrophy, injury of cauda equina, or myeleterosis;
7. being pregnant or breastfeeding;
8. with cardiac pacemaker, metal allergy or severe needle phobia;
9. unlike to give written formed consent.

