***sham EA group***

In sham EA group, participants were needled at sham BL33 and sham BL35, which were about 20 mm lateral to BL33 and BL35, respectively, with blunt needle tips piercing adhesive pads and not piercing the surface of the skin, using placebo needles of size 0.30×25 mm. Needles were then lifted, thrusted and twirled evenly for 3 times to achieve deqi. Paired electrodes of EA apparatus were attached transversely to bilateral sham BL33 and sham BL35 (using sham electrodes) respectively with same parameters and treatment courses.

To improve the effect of blindness, participants were informed that this trial was to compare the effects of two EA methods for pure SUI. One was traditional EA using conventional acupoints and electric current, and the other was non-traditional EA by needling on non-traditional acupoints with a weak electric current. The inform was approved by our ethics committee. Participants were discouraged from any other specialized treatments of SUI, mainly referring to SUI medications such as duloxetine, PFMT, feedback therapy, electrical or magnetic stimulation via pelvic floor, vagina or anus, and transcutaneous electrical nerve stimulation to pelvic floor. During the treatment period, if a participant was in her menstrual cycle, the treatment was postponed until the cycle ended. The length of delay was not included in the treatment period. It took 32 weeks in total for a patient to complete the trial: 1 week’s screening, 1 week’s baseline assessment, 6 weeks’ treatment, and 24 weeks’ follow up.

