**Outcome measures**

**Primary outcome:**

Change from baseline of urine leakage after 6 weeks measured by 1-hour pad test.

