**Second outcomes:**

1. Change from baseline of the mean 72-hour incontinence episode frequency (IEF) during weeks 1-6, weeks 15-18 and weeks 27-30;
2. Change from baseline of the total ICIQ-SF scores at weeks 6, 18 and 30;
3. Patient self-evaluation of therapeutic effect at weeks 6, 18 and 30.

Data of IEF was from 72-hour bladder diary. The bladder diary was recorded in detail the time and frequency of UI, activity that occurred at the time of leak, and the type and volume of liquid intake. In case that a participant was in her menstrual cycle or suffering from severe cough during an assessment week, she needed not to record the bladder diary until the end of cycle or the recovery of cough.

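### Carrying the last value forward scores a missing week-6 pad test as zero change, which shrinks the primary effect and can bias it if drop-out differs by arm

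*Protocol*

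**What the plan says.** The Sample Size and Statistical Analysis section sets one rule for all outcomes: "Missing data were filled in by the last observed value". The analysis set is everyone randomised: "All patients accepting randomization were included in the analysis". What the rule does depends on when each outcome is measured.

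- **Pad test (primary).** The endpoint is "Change from baseline of urine leakage after 6 weeks measured by 1-hour pad test". The only other pad test described is the one in the Participants section, where candidates "take 1 hour pad test by research assistants during 1-week baseline assessment to determine eligibility".
- **ICIQ-SF.** It is completed in the baseline week, and the outcome is "Change from baseline of the total ICIQ-SF scores at weeks 6, 18 and 30".
- **IEF.** The outcome is the change in "mean 72-hour incontinence episode frequency (IEF) during weeks 1-6, weeks 15-18 and weeks 27-30", from bladder diaries, with a baseline diary.
- **Self-evaluation.** The outcome is "Patient self-evaluation of therapeutic effect at weeks 6, 18 and 30". No baseline value exists.

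The course for each woman includes "6 weeks’ treatment, and 24 weeks’ follow up", so the assessments at weeks 15–18, 18, 27–30 and 30 all fall after treatment has ended. The sample size assumes 1.46 g with SD 1.74 g, two-sided alpha 0.05, 90% power and 20% drop-out. It arrives at 36 per group, raised to 40.

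**The concern.** With a baseline and one later pad test, carrying the last value forward is the same as carrying the baseline forward. Anyone who misses week 6 enters the primary comparison as a woman whose leakage did not change, whatever her arm. ICIQ-SF at week 6 is treated in the same way. For IEF, diaries kept during weeks 1–6 may supply a later value, so zero change does not necessarily follow.

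Four consequences are at stake:

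1. The primary difference is diluted even when drop-out is equal and random, and the mixture of zeros and real changes can widen the spread.
2. The sample size allows for drop-outs as patients lost, while the analysis keeps them at zero. The power calculation and the analysis therefore describe different things.
3. If drop-out differs between arms, the arm that loses more women has its mean pulled further toward zero, so the comparison can be biased in either direction.
4. For ICIQ-SF and IEF, a woman who leaves after week 6 has her on-treatment or end-of-treatment value carried into the follow-up that is meant to show whether benefit lasts.

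The rule also treats filled-in values as if they had been measured. For self-evaluation it has nothing to carry when week 6 is missing.

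**Working it through.** **Inputs from the protocol.** Difference 1.46 g, SD 1.74 g, two-sided alpha 0.05, power 90%, drop-out 20%, 1:1 allocation, 36 per group raised to 40. **Assumed, because the protocol does not give them:** the mean improvement *m* of sham completers (0 to 3 g) and any split of drop-out between arms.

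**1. The plan's own figure.** n = 2 × [1.74 × (1.960 + 1.282) / 1.46]² = 29.85, so 30 per group. Then 30 × 1.2 = 36, which reproduces the stated number. (Dividing by 0.8 gives 38, which 40 per group covers.) Either way the allowance treats drop-outs as lost.

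**2. Benchmark.** 40 × 0.8 = 32 completers per arm. Power for 1.46 g is 91% by t-test (92% by normal approximation).

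**3. Effect of scoring drop-outs as 0 g.** With drop-out proportion d and completer mean change M (M = *m* in sham, *m* + 1.46 in EA):

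- arm mean = (1 − d) M
- arm variance = (1 − d) SD² + d (1 − d) M²

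With d = 0.20 in both arms, the expected difference is 0.8 × 1.46 = 1.168, about 1.17 g, whatever the value of *m*.

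Example with *m* = 2:

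- EA variance = 0.8 × 3.0276 + 0.16 × 3.46² = 4.34
- sham variance = 0.8 × 3.0276 + 0.16 × 2² = 3.06
- standard error = √[(4.34 + 3.06) / 40] = 0.430
- 1.168 / 0.430 − 1.960 = 0.756, so power is about 77.5%

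Power at 40 per arm, 20% drop-out in each arm, two-sample t-test by simulation except in the second column:

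| Sham improvement (assumed) | Normal approx. | Random drop-out | Exactly 8 of 40 per arm |
|---|---|---|---|
| 0 g | 90% | 90% | 90% |
| 1 g | 86% | 85% | 88% |
| 2 g | 78% | 76% | 81% |
| 3 g | 67% | 66% | 71% |

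The last two columns differ only in whether the number of drop-outs is left to chance or fixed. With 10% random drop-out in each arm, power is about 93%, 91%, 88% and 82%.

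**4. Type I error, equal drop-out.** With no true effect and 20% random drop-out in both arms, rejection is about 5% across the range. With fixed counts it is 5% or lower.

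**5. Unequal drop-out, no true effect.** With 10% in EA and 30% in sham, the false difference is 0.9*m* − 0.7*m* = 0.2*m*:

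| Improvement in both arms (assumed) | False difference | Type I error, random | Type I error, fixed counts |
|---|---|---|---|
| 1 g | 0.20 g | 9% | 8% |
| 2 g | 0.40 g | 18% | 15% |
| 3 g | 0.60 g | 28% | 23% |

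Smaller imbalances do less. Under random drop-out, 10% EA / 15% sham gives 0.05–0.15 g and about 5–6.5%; 15% EA / 25% sham gives 0.10–0.30 g and about 6–10%.

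**6. Unequal drop-out, true effect 1.46 g, *m* = 2.** More loss in sham (10% EA / 30% sham): 0.9 × 3.46 − 0.7 × 2 = 1.71 g. More loss in EA (30% EA / 10% sham): 0.7 × 3.46 − 0.9 × 2 = 0.62 g. The bias runs both ways.

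**7. Follow-up and self-evaluation.** No arithmetic applies, because the protocol gives no drop-out rate after week 6 and no course of benefit after treatment. For self-evaluation, the first value is at week 6. If that is missing there is no earlier value, so the rule cannot deliver the all-randomised analysis that the same section promises.

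**The case against.** Several points on the other side have force.

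- **Equal drop-out is conservative.** If drop-out is similar in the two arms and unrelated to outcome, the rule works against EA and type I error stays near 5%. If sham completers do not improve, the power loss is only about one point (90% against 91%). This stands.
- **The larger harms rest on assumptions.** Neither the sham improvement nor a 10% / 30% split comes from the protocol, and milder splits do far less. This stands, so those figures show what could happen and are not forecasts.
- **Zero may be near the truth for some women.** If those who leave truly gained nothing, zero change is not far off. The rule, however, imposes that on every woman without a week-6 test, without giving it as a reasoned assumption.
- **The remedy also assumes something.** With no intermediate pad test, missing-at-random cannot be tested either. This is a reason for sensitivity analyses, not for keeping the present rule as the primary one.
- **This is a pilot** meant to explore efficacy, already enlarged to 40 per arm. That lowers the severity.

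A reader might infer that every early drop-out is scored as zero change on every outcome. The schedule supports that only for the pad test and ICIQ-SF. A reader might also infer that durability is overstated as a matter of course. That requires women to leave after week 6 and their benefit to wane, and a woman lost before week 6 has her baseline ICIQ-SF carried to weeks 18 and 30, which pulls the other way. Nor can sensitivity analyses be called absent from the trial, since a statistical analysis plan may exist. The point rests on the rule that the protocol does fix.

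**Conclusion.** The concern holds within limits. As written, the rule sets the primary change to exactly 0 g for any woman without a week-6 pad test. With 20% drop-out in each arm, unrelated to outcome, this shrinks 1.46 g to about 1.17 g, a fifth of the effect, and it does not match a sample size that treats drop-outs as lost. The power cost runs from about one point to about 25 points as the assumed sham improvement goes from 0 to 3 g.

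A general claim of an inflated false-positive rate is not supported: inflation needs drop-out that differs by arm or relates to outcome. Where it does differ, the bias can favour either arm. Overstated durability for ICIQ-SF and IEF is possible and conditional. The gap for self-evaluation follows directly from the schedule. Because the trial is an exploratory pilot and the worst figures depend on assumed inputs, this is something that should be fixed; it does not invalidate the design.

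**What to change.** Replace last-value-carried-forward as the primary rule, before unblinding.

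- **Pad test:** baseline-adjusted ANCOVA with multiple imputation under missing-at-random, with arm, baseline pad weight, IEF and ICIQ-SF as predictors.
- **ICIQ-SF and IEF over time:** a mixed model for repeated measures with baseline and arm by time.
- **Self-evaluation:** multiple imputation with a model suited to its scale. The protocol does not give the scale, so the model should be chosen once it is stated.
- **Sensitivity analyses:** zero change / last value carried forward, and a delta-adjusted analysis that makes the imputed outcomes progressively worse.

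The cost is a change of wording in the protocol or statistical analysis plan and a little more analysis work, with no new patients or data. The downside is reliance on the untestable missing-at-random assumption, which the sensitivity analyses are there to probe.

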**Methods**

**Study design**

This is a randomized, placebo-controlled study comparing EA with sham EA. Eighty women with pure SUI will be recruited from department of acupuncture and moxibustion of Guang’anmen hospital of China Academy of Chinese Medical Sciences (CACMS), Beijing, China. Participants will be randomly assigned to EA group or sham EA group by central randomization with a 1:1 ratio. The central randomization system was performed by the Clinical Evaluation Center of CACMS in Beijing. Random number and group assignment will be offered by telephone, mobile phone, or website from the Clinical Evaluation Center. In this study, participants, outcome assessors and statisticians are blinded to treatment allocation. This study was registered on ClinicalTrials.gov (Identifier: NCT02445573).

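### The primary comparison of change in pad-test leakage is unadjusted and not tied to the gram difference it was sized on; one prespecified ANCOVA on baseline pad weight would be a free gain in precision

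*Protocol*

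**What the plan says.** The protocol gives the primary outcome as "Change from baseline of urine leakage after 6 weeks measured by 1-hour pad test". In Sample Size and Statistical Analysis the trial is sized "to detect a between-group mean difference of 1.46 g (SD 1.74) in the reduction from baseline of urine leakage", so the planned effect is a difference between arms in mean change, in grams.

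The same section then says of the analysis that "Student t tests or Mann-Whitney U tests were used for the comparison of continuous variables", each to be used where appropriate. No covariate is named, and no single test or effect measure is fixed for the primary outcome. On summaries, "Continuous data were presented with mean and standard deviation [M (SD)] if they were normally distributed", and otherwise median and interquartile range are given. No normality test or decision rule is stated.

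Under Participants, a 1-hour pad test is part of the baseline assessment that determines eligibility. Entry requires a gain above 1 g, and no upper limit is given. A baseline value therefore exists for everyone randomized.

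**The concern.** Subtracting the baseline is not the same as adjusting for it. Leakage cannot fall below zero, so the possible reduction is capped by the starting value. As an illustration, a woman who enters at 2 g can improve by at most 2 g, while one who enters at 20 g can improve by much more. Change is then likely to depend on baseline. With 40 per arm, a chance difference in baseline pad weight passes partly into the raw comparison of change, and the variation that baseline explains stays in the error term.

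The second issue is the effect measure. The sample size rests on a mean difference in grams, which a Mann-Whitney test neither tests nor estimates. If the rank test were used and the data summarised by medians, the trial might report no estimate of the quantity it was planned to detect.

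**Working it through.** **Inputs from the protocol.** Two-sided alpha 0.05, power 90%, drop-out 20%, difference 1.46 g, SD of change 1.74 g, 36 per group needed, 40 per group planned, 1:1 allocation.

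**Inputs assumed.** The correlation r between baseline and week-6 pad weight is not given; I use 0.3 to 0.9. I take the SD s of pad weight as equal at the two visits.

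**1. The plan's own figure.** n per group = 2 × [1.74 × (1.960 + 1.282) / 1.46]² = 29.85, so 30 evaluable. 30 × 1.2 = 36, as stated. Dividing by 0.8 instead gives 37.5, so 38. The planned 40 covers both.

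**2. Power without adjustment at 1.46 g (normal approximation).** 91.9% with 32 per arm (40 × 0.8) and 96.3% with 40 per arm. The noncentral t gives 91.1% and 96.0%. The 90% target is met either way.

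**3. Variance ratio.** Change has variance 2s²(1 − r). ANCOVA has residual variance s²(1 − r²). The ratio is (1 + r)/2.

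**4. Precision.** Half-width = 1.96 × 1.74 × √(2/n) × √ratio. Unadjusted (ratio 1), this is 0.853 g for n = 32 and 0.763 g for n = 40.

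| r (assumed) | Ratio | Variance cut | Half-width, 32 per arm | Half-width, 40 per arm | Power at 1.46 g, 32 per arm |
|---|---|---|---|---|---|
| unadjusted | 1 | – | 0.85 g | 0.76 g | 91.9% |
| 0.3 | 0.65 | 35% | 0.69 g | 0.61 g | 98.6% |
| 0.5 | 0.75 | 25% | 0.74 g | 0.66 g | 97.2% |
| 0.7 | 0.85 | 15% | 0.79 g | 0.70 g | 95.4% |
| 0.9 | 0.95 | 5% | 0.83 g | 0.74 g | 93.1% |

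If the week-6 SD is smaller than the baseline SD, the gain is larger. At a week-6 SD 0.7 times the baseline SD, the ratio is 0.42, 0.47 and 0.49 for r = 0.3, 0.5 and 0.7.

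**5. Chance imbalance.** With SD of change 1.74, s = 1.74/√[2(1 − r)]. A baseline difference of one standard error, s√(2/40), shifts the raw comparison by (1 − r) × s × √(2/40). That is 0.23, 0.19, 0.15 and 0.09 g at r = 0.3, 0.5, 0.7 and 0.9. The shift is conditional on the imbalance; averaged over randomizations it is zero.

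**6. Having two tests available.** These are simulations with 40 per arm; the distributions and the Shapiro-Wilk rule are assumed.
- Normal data, no difference: t 4.9%, Mann-Whitney 4.7%, switching by the fixed rule 5.0%. The two tests disagree at P<0.05 in 2.2% of trials.
- Skewed (log-normal) data, identical in both arms: t 3.8%, Mann-Whitney 4.3%, fixed rule 4.3%. The tests disagree in 4.5% of trials.
- Rejection by either test = (t + Mann-Whitney + disagreement)/2. This gives about 5.9% and 6.3% in these two cases. A separate skewed simulation gave (5.2 + 5.2 + 4.25)/2 = 7.3%.
- Skewed data with equal means but one SD half the other: t rejects in 7.1% of trials, Mann-Whitney in 57.3%. The tests answer different questions there, so this is not an error rate for the rank test's own hypothesis.

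**The case against.** The strongest reply is that nothing stated is wrong. An unadjusted comparison of change is valid when "Participants will be randomly assigned to EA group or sham EA group by central randomization with a 1:1 ratio", the power target is met without a covariate, and a statistical analysis plan, not shown here, may settle the model. The study also calls itself a pilot. All of this stands, and it limits the point to an improvement. It does not remove the point, because the protocol does set out its analysis methods and names only unadjusted, interchangeable tests.

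Several stronger readings are tempting but not supported:
- **That baseline is ignored.** It is subtracted in the outcome; it is only not used as a covariate.
- **That the target of estimation is open.** Variable and time point are fixed, and the sample size implies a mean difference in grams. What is missing is a commitment to that measure in the analysis text.
- **That the protocol prescribes choosing the test from the observed distribution.** The normality condition governs how data are presented. Its extension to the tests is a reasonable inference, not a stated rule.
- **That type I error is inflated to 7%.** That needs free choice between the two results. Under a fixed rule it stays near 5% when the arms do not differ, and the Study design section blinds the statisticians to allocation.
- **That the trial would usually end on a rank test.** This depends on an assumed skewed distribution; the protocol gives none.

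One further limit: the precision gains in the table use normal-theory formulas. The gain from ANCOVA on the gram scale under strong skew was not computed.

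**Conclusion.** The point holds as a free improvement, not as an error in a stated number. The protocol's primary comparison leaves unused a covariate that is already collected, and does not bind itself to the gram difference behind its sample size.

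The size depends on a correlation the protocol does not give. With equal SDs and r from 0.3 to 0.9, adjustment removes 35% down to 5% of the variance. At the 40 per arm that the intention-to-treat analysis with carried-forward values would use, this narrows the half-width by 0.15 g at most (0.76 to 0.61 g) and 0.02 g at least (0.76 to 0.74 g). A reader should not infer that the trial is underpowered for 1.46 g or that its planned test is invalid.

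**What to change.** In Sample Size and Statistical Analysis, name one primary analysis that applies whatever the distribution: ANCOVA of week-6 pad weight (or its change) on arm and baseline pad weight. Report the adjusted mean difference in grams with a 95% CI, using robust standard errors or permutation inference so that skew gives no reason to switch tests. Keep the Mann-Whitney test, or ANCOVA on a log scale, as a named sensitivity analysis. The same baseline adjustment for incontinence episode frequency and ICIQ-SF is optional.

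The cost is a sentence or two of text. No extra participants, visits or measurements are needed, and the planned 40 per group can stay as it is.

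### The primary pad test falls under both between-group and within-group paired tests at P<0.05; the plan does not call the paired tests descriptive or name the between-group test as the efficacy test

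*Protocol*

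**What the plan says.** The design is comparative. Under Study design the protocol states: "This is a randomized, placebo-controlled study comparing EA with sham EA". Allocation is 1:1. The primary outcome is given as "Change from baseline of urine leakage after 6 weeks measured by 1-hour pad test", and no other pad-test time is listed.

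The section Sample Size and Statistical Analysis sizes the trial on a contrast between arms: "to detect a between-group mean difference of 1.46 g (SD 1.74) in the reduction from baseline of urine leakage measured by 1-hour pad test". The same section then gives two rules for continuous data. The first uses Student t or Mann-Whitney U tests to compare continuous variables. The second reads: "For measures collected at two time points, paired t-tests or Wilcoxon signed rank tests were used as appropriate". The next sentence sets a significance level of P<0.05 without distinguishing between the two.

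Under Participants, the diagnostic criteria require a pad weight gain of more than 1 g. Candidates "take 1 hour pad test by research assistants during 1-week baseline assessment to determine eligibility", so the entry test is done in the baseline week.

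**The concern.** The pad test is the only listed continuous outcome with exactly two time points. The ICIQ-SF score and the incontinence episode frequency each have three assessments after baseline. The paired-test sentence therefore fits the primary outcome better than any other efficacy measure, and it attaches a before/after P value to it.

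That P value does not answer the trial's question. A paired test asks whether leakage changed within an arm. It cannot separate an effect of EA from placebo response, natural course or regression to the mean. The last is a live possibility here, because readings of 1 g or less are excluded at baseline but not at week 6.

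The stake is interpretation. A report could show a significant change with EA beside a non-significant change with sham, or significance in both arms, and either could be taken as evidence of efficacy although neither compares the arms. Nothing in the protocol rules this out.

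**Working it through.** **Inputs from the protocol:** two-sided alpha 0.05; power 90%; drop-out 20%; difference 1.46 g; SD 1.74 g; 36 per group required, 40 per group planned. **Assumption, not in the protocol:** both arms improve by the same mean amount, so the true EA-minus-sham difference is zero. That amount is varied from 0.25 to 1.46 g. The SD of change is taken as 1.74 g in each arm, changes as normal and the arms as independent.

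**1. The plan's own figure.** The two-sample formula is n = 2 × (1.960 + 1.282)² × (1.74/1.46)² = 2 × 10.51 × 1.420 ≈ 29.9, so 30 per arm. Adding 20% gives 30 × 1.2 = 36, the stated number. (Dividing by 0.8 would give 38; the planned 40 covers either.) The figure is therefore reproduced as a between-group comparison of change, with 1.74 g as the SD of change within each arm.

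**2. Significance threshold for a paired t test within one arm.** The standard error is 1.74/√40 = 0.275 g and t(0.975, 39 df) = 2.023. The threshold is 2.023 × 0.275 ≈ 0.56 g. Any larger mean reduction in an arm gives P<0.05, whatever the other arm does.

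**3. How often this happens with no treatment difference.** For a common improvement m, the noncentrality is m/0.275. The probability p of a significant improvement in a given arm comes from the noncentral t distribution with 39 df. Significance in EA but not in sham has probability p(1 − p); significance in both arms has probability p².

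| Common improvement m (assumed) | p, given arm | EA only, p(1 − p) | Both arms, p² |
|---|---|---|---|
| 0.25 g | 14% | 12% | 2% |
| 0.5 g | 43% | 24% | 18% |
| 0.75 g | 76% | 18% | 57% |
| 1.0 g | 94% | 5% | 89% |
| 1.46 g | 99.9% | 0.1% | over 99% |

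The two-sample test would falsely favour EA 2.5% of the time in every row. From 0.25 to 1.0 g the EA-only pattern is thus about 2 to 10 times as frequent (5.3/2.5 ≈ 2; 24.4/2.5 ≈ 10). At 1.46 g it almost disappears, because both arms are then nearly always significant.

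**4. With 32 per arm** (40 × 0.8), p is 12%, 35%, 66%, 88% and 99.6%, so the picture is similar.

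**5. Power of the between-group test.** For 1.46 g with SD 1.74 g, the two-sample t test has about 96% power with 40 per arm and about 91% with 32. Resting efficacy on this test alone costs no patients.

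**The case against.** The strongest reply is that the protocol already has a between-arm test. Change from baseline is one continuous value per patient, so the two-sample rule covers it. The sample size is a two-sample calculation on that change, and the stated aim is EA against sham. On this reading the paired tests are a supplementary before/after description and leave the validity and power of the between-arm test untouched. This stands. A reader who saw only the paired-test sentence might infer that the plan lacks a randomised comparison, or that efficacy will be judged on the paired tests. The protocol supports neither inference.

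A reader might also infer that the paired tests will show improvement in both arms. That is too strong. The protocol gives no expected change under sham, and the probability in a given arm runs from 14% to over 99% across the assumed range. Nor can regression to the mean be sized, since neither the distribution of pad weights nor the repeatability of the test is given.

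A third reply is that ranking the tests belongs in a statistical analysis plan, which may exist. That would answer a complaint about missing detail. Here the protocol itself assigns an inferential test at P<0.05 that does not address its own question, and an analysis plan that followed this sentence would carry it forward.

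Finally, an unadjusted two-sample comparison of change is valid under randomisation, so baseline adjustment is not needed to cure the ambiguity. That is correct. Adjustment is recommended because the baseline pad weight is already collected and using it generally improves precision.

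**Conclusion.** The point holds as an ambiguity with a practical risk. Two families of test apply to the primary outcome, neither is designated as the efficacy test, and the one that ignores randomisation is not limited to description. The intended contrast is almost certainly between groups, but the text does not commit to it.

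The size of the risk depends on an improvement common to both arms that the documents do not give. For 0.25 to 1.0 g, the misleading EA-only pattern arises 5% to 24% of the time under no treatment difference, against 2.5% for a two-sample result falsely favouring EA. For larger common changes the likely result is significance in both arms. These figures rest on the protocol's SD of 1.74 g applying in each arm, 40 patients per arm and approximately normal changes. The planned between-group comparison is not itself in doubt. The wording should be corrected.

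**What to change.** Remove the paired t and Wilcoxon signed rank tests as tests of effect. Report within-arm change descriptively, as mean change with a 95% CI and no P value.

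State that the only primary efficacy test is the EA-minus-sham difference in pad-test change from baseline to week 6, estimated by ANCOVA with baseline pad weight as covariate and reported with its 95% CI. Add that no efficacy statement will rest on significance within an arm, or on significance in one arm and not the other.

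The cost is a change of wording and a small change of analysis model, from a two-sample test to ANCOVA. No new data and no extra patients are required.
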